### Study Aims and Hypotheses

Specific hypotheses to be tested in this study are that:

Consumers using a Web-based PCHMS with interactive and social features are more likely to follow evidence-based guideline recommendations for asthma management, as measured by the rates of obtaining or updating a written asthma action plan with their GP and the usage rates with the asthma action plan, measured by questionnaires;Use of a PCHMS will contribute to improved asthma control and reduced rates of asthma exacerbation compared to those using only static websites (usual care arm).

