**Secondary outcomes**					
	Number of participants reported using their written asthma action plan, obtained, or updated during the study	Post-study survey	X		X
	Rate of planned (non-urgent) visits to a healthcare professional (eg, GP) for routine asthma management	Post-study survey			X
	Rate of unplanned visits to a GP, emergency department, caused by worsening asthma	Post-study survey			X
	Website usage patterns (number and timing of hits, duration of access, uptake of specific functions) of *Healthy.me*	*Healthy.me* system logs			X
	Technology acceptance of *Healthy.me*	Measured via the “Scales for Perceived Usefulness and Perceived Ease of Use” [30]			X
	Asthma control	Measured via “Asthma Control Questionnaire” [31]		X	
	Asthma exacerbations	Measured via the “Asthma Exacerbation Questionnaire” [32]		X	
	Number of days lost from work or school	Measured via an additional question after the “Asthma Control Questionnaire” [31]		X	
	Competing demands on health and asthma	Lists of life priorities and top health issues, monthly made by participants.		X	
					
					
					

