#### Secondary and Ancillary Analysis

Differences in proportions of participants between different groups (eg, control vs. PCHMS) will be examined using χ^2^test based on data collected from pre-, monthly, and post-intervention questionnaires, for each of the following activities experienced at least once during the study: (1) visited a GP (or a healthcare professional) for an unplanned asthma visit; (2) used medications or remedy; and (3) experienced performance impairment. Differences in average number of days of absence per participant and differences in score distributions from questionnaires will be compared between control and PCHMS groups using Student’s *t*-test or non-parametric statistics. Reasons for receiving (or not receiving) written asthma action plan will be reported using descriptive statistics. Attrition rate for the use of *Healthy.me* will be assessed with system logs. Technology acceptance of *Healthy.me* will be measured via the “Scales for Perceived Usefulness and Perceived Ease of Use” [30,38]. Participants’ satisfaction and utilization of Healthy.me will be reported. Cost effectiveness of health service utilization [39] (upon availability and feasibility) will also be considered as well as economic costs from days lost from work/school. If any post-hoc comparison would need to be performed between unplanned groups of participants, a Holm’s sequential Bonferroni procedure [40] will be used in order to control a familywise error rate *FWER* inferior or equal to level α = .05.

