### Study Procedure

Table 3 below summarizes participant procedures in the study. The duration of the study is expected to be 12 months.

Email will be the primary channel to communicate with participants for study information and reminders about survey completion. From the time participants are recruited until study completion, all participants (control and intervention) will receive an email each month to complete a 5-minute survey about their health in the past month. At study completion, all participants will receive an email asking them to complete a post-study survey. In order to ensure the completeness of data collection, there will be 2 follow-up emails sent 5 days apart from each other to remind those who have not completed each survey.

**Table 2 table2:** Surveys used in the study.

Survey	Purpose
Screening survey	Eliciting participants’ eligibility criteria.
Pre-trial survey	To obtain participants’ demographics and experiences of asthma management at study enrolment.
Monthly follow-up questions	To obtain participants’ self-reported symptoms of asthma (ie, asthma control and exacerbation), impact on work and study due to asthma symptoms, and competing demands and health throughout the study.
Post-trial survey (12 months after the beginning of the study)	To obtain participants’ state of asthma control and asthma management. For those who receive the PCHMS version of *Healthy.me*, their perceived usefulness of *Healthy.me* will also be assessed.

**Table 3 table3:** Stages of study procedure.

Stage of study	Procedure

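### Asthma control and exacerbations (Hypothesis 2) have no baseline score and an unadjusted comparison, which costs precision; separately, at-least-once outcomes depend on how many monthly surveys are returned

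*Protocol article*

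**What the plan says.** Study Aims and Hypotheses sets out the second hypothesis: "Use of a PCHMS will contribute to improved asthma control and reduced rates of asthma exacerbation compared to those using only static websites".

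Table 1 lists asthma control (by the "Asthma Control Questionnaire"), asthma exacerbations and days lost from work or school. Each is marked in the Monthly column only. Table 2 agrees on the baseline: the pre-trial survey serves "To obtain participants’ demographics and experiences of asthma management at study enrolment", while control and exacerbation appear under the monthly questions. Table 2 also has the post-trial survey record the state of asthma control, which Table 1 does not mark at completion.

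Secondary and Ancillary Analysis says that "Differences in average number of days of absence per participant and differences in score distributions from questionnaires will be compared" between arms by Student's t-test or a non-parametric test. It does not say which month or summary is tested. Covariate adjustment and a missing-data rule (LOCF) are stated only under Primary Analysis.

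The same section applies chi-square tests "for each of the following activities experienced at least once during the study": an unplanned visit, use of medication or a remedy, and impaired performance. The data are to come from the pre-study, monthly and post-study questionnaires. Table 1 instead defines a "Rate of unplanned visits to a GP, emergency department, caused by worsening asthma" and takes it from the post-study survey alone.

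**The concern.** There are two separate issues.

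The first is a matter of data collection. A score that is never collected at baseline cannot be adjusted for later, whatever a statistical analysis plan says. The only related baseline measure named is the two-level severity stratum (intermittent or persistent) under Randomization. The first monthly survey cannot stand in, because monthly surveys run from recruitment onwards and allocation is revealed once the pre-study questionnaire is done. A stated hypothesis would therefore be tested with less information than an existing 10-minute pre-study survey could supply.

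The second concerns the at-least-once outcomes. If monthly surveys feed them, a participant who returns more surveys has more chances to report an event. The arms could then differ only because survey return differs. Limitations foresees high attrition, and Concluding Remarks expects the social and interactive features, which only the intervention arm has, to reduce attrition. That remark may refer to platform use and not to survey return, but it makes a difference between arms plausible. If the intervention arm returned more surveys, the distortion would run against the intervention. Reducing events to any or none also discards the count, although Table 1 speaks of a rate.

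**Working it through.** The document gives no power, correlation, event risk or return rate for these outcomes, so there is no figure of the plan to reproduce here. The sample size of 300 belongs to the primary outcome. From Sample Size I take 150 per arm and 25% dropout: 150 × 0.75 = 112.5, so 112 per arm. Correlations, monthly risks and numbers of surveys returned are assumptions, shown over a range.

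**1. Value of a baseline score**

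Take 12 monthly scores, each with variance 1, and equal correlation ρ between all scores including baseline (compound symmetry).

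- Variance of the 12-month mean: (1 + 11ρ)/12.
- After baseline adjustment: (1 + 11ρ)/12 − ρ².
- Detectable difference at 80% power, two-sided 5%: (1.96 + 0.84) × √(2 × variance/112), in SD of a single score.

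| ρ | 12-month mean | with baseline | variance cut | detectable difference |
|---|---|---|---|---|
| 0.4 | 0.450 | 0.290 | 36% | 0.25 → 0.20 |
| 0.5 | 0.542 | 0.292 | 46% | 0.28 → 0.20 |
| 0.6 | 0.633 | 0.273 | 57% | 0.30 → 0.20 |
| 0.7 | 0.725 | 0.235 | 68% | 0.32 → 0.18 |
| 0.8 | 0.817 | 0.177 | 78% | 0.34 → 0.16 |

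The cut reaches half when ρ² = (1 + 11ρ)/24, that is 24ρ² − 11ρ − 1 = 0, so ρ = (11 + √217)/48 ≈ 0.54.

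If correlation instead decays with time (AR(1)), the variance goes from 0.491 to 0.395 at 0.8 (20% cut), from 0.686 to 0.397 at 0.9 (42%), and from 0.824 to 0.294 at 0.95 (64%).

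These figures compare with no adjustment at all. Adjusting for the severity stratum would recover part of the gain. They apply most directly to the control score, and less directly to skewed counts such as days lost.

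**2. At-least-once outcomes under unequal survey return**

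With monthly risk q in both arms and m surveys returned, the proportion with at least one report is 1 − (1 − q)^m. At q = 5%:

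- 10 against 8 surveys: 1 − 0.95^10 = 40.1% and 1 − 0.95^8 = 33.7%, a gap of 6.5 points before rounding. With 112 per arm, the chance of a significant result with no true effect is 17%.
- 11 against 7 surveys: 43.1% and 30.2%, a gap of 13 points, with a false-positive rate of 52%.
- 9 against 9 surveys: no gap, and the rate is 5%.

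Over q from 3% to 10%, the false-positive rate is 13% to 24% for 10 against 8, and 37% to 71% for 11 against 7.

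**3. Information lost by any-or-none**

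If events follow a Poisson distribution with mean λ per participant, the efficiency of any event relative to the count is λe^(−λ)/(1 − e^(−λ)). This gives 86%, 73%, 52% and 24% at λ = 0.3, 0.6, 1.2 and 2.4.

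**The case against.** The strongest reply is that these are secondary outcomes in a condensed article, and that the choice between a summary t-test and a longitudinal model, the use of offsets and the secondary missing-data rule are commonly left to an analysis plan. That stands for the modelling detail. It does not cover the absent baseline measurement, nor the tests that the article does name.

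Several stronger readings are tempting, and the document does not support them.

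- *The missing baseline biases the result.* It does not. Allocation is random and stratified by severity, so the comparison stays valid.
- *Most of the precision is lost.* Against a 12-month mean under equal correlations, this holds only above about 0.54. A single-month t-test would lose more (71% to 82% of variance), but the article does not say that one month is used. With complete data and equal correlations, a t-test on the 12-month mean loses nothing against a repeated-measures model without baseline.
- *Hypothesis 2 itself is reduced to at-least-once proportions.* It is not. The three items so treated are other outcomes.
- *Survey return will differ by arm.* No return rates are given, and both arms get the same emails and reminders. If unplanned visits come only from the post-study survey, as Table 1 has it, the number of monthly surveys returned cannot affect them. Access of 9 to 12 months, stated for the intervention group, does not by itself show unequal follow-up either, since the arms run concurrently.
- *Nearly everyone will report medication use.* This is plausible, but no figure supports it, and the trial has an intermittent-asthma stratum.

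**Conclusion.** The point holds in two limited parts and is worth acting on, at the weight of a secondary hypothesis.

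First, asthma control, exacerbations and days lost have no scheduled baseline score, and the comparison named for them is unadjusted. The cost is precision and not validity. Its size rests on unstated correlations: 36% to 78% of the variance of a 12-month mean for equal correlations of 0.4 to 0.8, or 20% to 64% under AR(1) with 0.8 to 0.95. Tables 1 and 2 agree on the missing baseline, so this part is firm.

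Second, the at-least-once outcomes drop the rate that Table 1 defines for unplanned visits. They are also open to distortion wherever monthly surveys supply the data and return differs between arms. This part is conditional: the gap is zero with equal return, and about 6.5 points at an assumed 5% monthly risk with 10 against 8 surveys.

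The document also disagrees with itself on the source of unplanned visits (Table 1 against Secondary and Ancillary Analysis) and on whether asthma control is measured at completion (Table 1 against Table 2).

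**What to change.** 1. Add the Asthma Control Questionnaire, with prior-month exacerbation and absence items, to the existing pre-study survey.
2. Analyse monthly control scores with a repeated-measures model adjusted for baseline and the randomisation strata (gender and severity). Model baseline as part of the outcome vector, or impute it. Entered as an ordinary covariate, it would drop participants enrolled before the change, and the article says that recruitment is already under way.
3. Analyse exacerbations, unplanned visits and days lost as counts, with log(months reported) as offset, where the questionnaires yield counts. State the missing-at-random assumption, since an offset does not correct for non-return that depends on the outcome.
4. Reconcile Table 1, Table 2 and Secondary and Ancillary Analysis on which survey supplies unplanned visits and end-of-study asthma control.

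The cost is a few more online survey items, more analysis work, and no baseline score for those already enrolled.

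### Asthma control and exacerbation scores are collected monthly, but the two-sample test named for them does not fix the unit or time point

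*Protocol article*

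**What the plan says.** All places are in the protocol article.

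- **Study Aims and Hypotheses.** The second hypothesis reads: "Use of a PCHMS will contribute to improved asthma control and reduced rates of asthma exacerbation compared to those using only static websites".
- **Table 1, secondary outcomes.** Asthma control is "Measured via “Asthma Control Questionnaire” [31]" and exacerbations are "Measured via the “Asthma Exacerbation Questionnaire” [32]". Both rows are marked in the Monthly column only.
- **Study Procedure.** The schedule applies to both arms: "all participants (control and intervention) will receive an email each month to complete a 5-minute survey about their health in the past month".
- **Table 2.** The post-trial survey at 12 months is also meant to capture the participant's "state of asthma control and asthma management". Table 1 marks no completion reading for asthma control.
- **Secondary and Ancillary Analysis.** For the scores, "differences in score distributions from questionnaires will be compared between control and PCHMS groups" using Student's t-test or non-parametric statistics. For days of absence, the same sentence names an average per participant. For the scores it names no summary, no month and no model for repeated values.
- **Intervention Group and Exposure.** Access lasts 9 to 12 months depending on registration date, so the number of monthly records per person may differ.
- **Randomization.** Allocation is stratified by gender and asthma severity. The score comparison as stated does not adjust for these strata.

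**The concern.** A two-sample t-test or rank test assumes one independent value per participant. Here each participant may supply 9 to 12 correlated scores on each questionnaire, so the scores must be reduced to one value or modelled jointly before the test has a definite meaning. The article names the test but not the reduction. Several analyses fit the wording, and they differ in power, in error rate and in sensitivity to missing months.

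For the asthma control score this is the only between-arm test stated. The chi-square list in the same section covers unplanned visits, use of medication or remedy, and performance impairment. The test therefore carries the asthma-control part of the second hypothesis. If the unit and time point are settled only after the data are seen, the result can depend on that choice.

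**Working it through.** The article gives no SD, target effect or within-person correlation for these scores, so it has no figure of its own to reproduce here. The stated sample size concerns the primary outcome only.

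**Inputs from the article.** 150 per arm and about 25% dropout (Sample Size): 150 × 0.75 = 112.5, taken as 112 per arm. Monthly scores per person: m = 9 to 12. Two-sided test at 5%.

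**Assumptions, not in the article.** Equal correlation ρ between any two monthly scores of one person, 0.5 to 0.7; a constant between-arm difference of 0.3 SD; complete months.

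**Formulas.**
- Design effect: DE = 1 + (m − 1)ρ. For m = 12 it is 6.5, 7.6 and 8.7 at ρ = 0.5, 0.6 and 0.7.
- Variance of a person mean relative to one score: DE/m. For m = 12 it is 0.542, 0.633 and 0.725.
- Power: Φ(0.3 / √(2v/112) − 1.96), with v = 1 for one month and v = DE/12 for the mean.
- Type I error if all person-months are treated as independent: 2[1 − Φ(1.96/√DE)].

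**Reading 1, one month per person.** 0.3/√(2/112) = 2.245, and Φ(2.245 − 1.96) = 0.61. The type I error stays at 5%.

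**Reading 2, mean of 12 months per person.** At ρ = 0.5: 2.245/√0.542 = 3.05, giving power 0.86. At ρ = 0.6: 0.81. At ρ = 0.7: 0.75. In simulations of this test (4,000 runs each), the type I error was 0.046, 0.052 and 0.050 at ρ = 0.3, 0.5 and 0.8.

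**Reading 3, a separate test each month.** With 12 equally correlated z-tests, the chance of at least one false positive is 0.32, 0.28 and 0.23 at ρ = 0.5, 0.6 and 0.7. The Holm procedure in the article is limited to post-hoc comparisons between unplanned groups, so it would not cover these tests.

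**Reading 4, all person-months pooled.** With m = 12 the type I error is 0.44, 0.48 and 0.51; with m = 9 it is 0.38, 0.42 and 0.45.

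| Reading | Type I error | Power at 0.3 SD |
|---|---|---|
| One month | 5% | 61% |
| 12-month person mean | about 5% | 75% to 86% |
| 12 monthly tests | 23% to 32% (any) | – |
| Pooled, 12 months | 44% to 51% | – |

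**Missing months.** These figures assume complete data. Limitations names high attrition as a possibility. Concluding Remarks expects the social and interactive features, which only the intervention arm receives, to reduce attrition. The article also treats season as a shared environmental condition of the concurrent arms. If one arm loses more late months, or loses them in relation to symptoms, simple person means in the two arms average over different months and may not be comparable.

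**The case against.** The strongest reply is that the named test is not wrong. A t-test or rank test on a per-participant mean fits the wording, keeps the type I error near 5% and uses every score. The surrounding text leans that way: days of absence, also a monthly item, are averaged per participant, and the chi-square comparisons reduce the survey data to whether an event occurred at least once. This stands. The 75% to 86% power above comes from exactly that test, so it shows the gain from using all months, not a gain of a mixed model over a person mean.

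A reader might infer that the second hypothesis will be tested either with false precision or with most of the data unused. The document does not support this. It nowhere says that person-months will be pooled, that twelve tests will be run or that one month will be picked. Even the single-month reading is a loss of efficiency, not an error.

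A reader might also infer that a person mean is valid only if both arms return the same months. That is too strict. Unequal numbers of months mainly affect precision; bias needs missingness that differs by arm and relates to the score or its time course. The article calls high attrition possible, not certain, and plans reminders. A mixed model needs a missing-at-random assumption of its own.

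Finally, this is a condensed article, and an analysis plan that is not shown may define the summary and the handling of missing months. That lowers the weight of the point. It does not remove it, because the test the article does commit to is open to readings with very different properties. The difference between Tables 1 and 2 is likewise only a point to clarify: the 12-month item is described generally and need not be the Asthma Control Questionnaire.

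**Conclusion.** The point holds in a limited form. The article names a two-sample test for monthly scores without fixing the per-participant value or time point, and makes no use of the repeated structure or the randomisation strata. Under valid readings, power for a 0.3 SD effect runs from about 61% (one month) to 75% to 86% (12-month mean). The inflated error rates of 23% to 51% belong to readings that the wording does not exclude but does not state, so they are not a forecast of what the trial will do. Bias from unequal loss of months is plausible on the article's own account, but its size cannot be derived from the document.

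All magnitudes depend on the assumed correlation, effect size and 112 evaluable per arm. The outcomes are secondary, so severity is modest; confidence is moderate.

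**What to change.** In Secondary and Ancillary Analysis, analyse the monthly asthma control score with a linear mixed model for repeated measures. Include arm, month, arm-by-month, the randomisation strata (gender and asthma severity) and within-person correlation. Name one contrast in advance: the average between-arm difference over follow-up.

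For exacerbations, use a repeated-measures or rate model suited to the scale of the outcome, since the hypothesis is framed in rates. A pre-specified per-participant mean adjusted for the strata is an acceptable simpler alternative; it stays closest to the stated test and should come with a rule for missing months.

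State whether the 12-month asthma control item in Table 2 is the Asthma Control Questionnaire, and make Table 1 agree.

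The cost is wording and a little more analysis, with no new data. The downside is that a covariance structure must be chosen and the model relies on missingness at random. The change should be fixed before group allocation is revealed to the analysts.

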### Study Procedure

Table 3 below summarizes participant procedures in the study. The duration of the study is expected to be 12 months.

Email will be the primary channel to communicate with participants for study information and reminders about survey completion. From the time participants are recruited until study completion, all participants (control and intervention) will receive an email each month to complete a 5-minute survey about their health in the past month. At study completion, all participants will receive an email asking them to complete a post-study survey. In order to ensure the completeness of data collection, there will be 2 follow-up emails sent 5 days apart from each other to remind those who have not completed each survey.

**Table 2 table2:** Surveys used in the study.

Survey	Purpose
Screening survey	Eliciting participants’ eligibility criteria.
Pre-trial survey	To obtain participants’ demographics and experiences of asthma management at study enrolment.
Monthly follow-up questions	To obtain participants’ self-reported symptoms of asthma (ie, asthma control and exacerbation), impact on work and study due to asthma symptoms, and competing demands and health throughout the study.
Post-trial survey (12 months after the beginning of the study)	To obtain participants’ state of asthma control and asthma management. For those who receive the PCHMS version of *Healthy.me*, their perceived usefulness of *Healthy.me* will also be assessed.

**Table 3 table3:** Stages of study procedure.

Stage of study	Procedure

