## Methods

### Study Design

A randomized controlled trial with a 2-group parallel design (with intervention allocation ratio 1:1) will be used to evaluate the efficacy of the Web-based PCHMS *Healthy.me*, reported in accordance to the 2010 CONSORT statements [27](ACTRN12612000716864). The PCHMS is not part of usual care but aims to improve usual care as measured by compliance to evidence-based guidelines.

Participants randomized to the *intervention* group will have immediate access to an interactive version of *Healthy.me* with full PCHMS features as described later, from the date they are recruited.Participants randomized to the *control* group will receive access to a static webpage, without PCHMS features or any interactive component. This webpage will offer links to Australian information websites about asthma.

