### Sample Size

A conservative estimate of at least 300 participants with 150 in each arm is needed to detect a 15% point difference in possession rate of a written asthma action plan between the control group (14.4%) and the intervention group (29.4%). This estimate is calculated at 5% level of significance, 80% power (2-sided test), with an anticipated participant dropout rate approximately 25%.

The effect size estimate is based on previous studies using *Healthy.me* assessing the efficacy of Internet-based interventions on the uptake of preventative health actions [23], and on studies with interventions promoting the use of personal asthma action plans [13]. The base rate is the percentage of adults (ie, 15 years and over) with current asthma in Australia and possessing a written asthma action plan, reported in the Australia Centre for Asthma Monitoring analysis of the Australian Bureau of Statistics National Health Survey 2007-2008, and cited in the Australia Centre for Asthma Monitoring 2011 report [2].

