## Discussion

### Limitations

There are several potential limitations in this study. Firstly, the number of participants meeting inclusion criteria at study completion might be low because the study will focus recruitment only in Australia. The other inclusion criteria such as age, Internet access, and English speaking skills, might be also restrictive for recruiting participant in the targeted population.

Secondly, there is a possible high attrition rates*.* The study’s outcomes will rely on data from participants’ self-reports. Due to the long duration of the study, over 12 months, it is possible to observe a high rate of attrition from participants and thus, a significant loss of data. To limit this, all participants will be actively requested to complete questionnaires by receiving monthly reminders via emails. Furthermore, the questionnaires used on a monthly-basis will be easy and convenient complete (short questionnaires with an online completion using multiple-choice questions).

Thirdly, there may not be representative of consumers with asthma. The study may be more appealing to younger participants who are interested or literate in computers, the Internet, or asthma self-management topics. These participants may be more enthusiastic about health and the Internet than the general asthma population.

Fourthly, as this is a pragmatic trial of a multifaceted intervention in a complex environment, it is possible that baseline variables associated with participants might also influence the outcome. For example, having a prior history of obtaining a written asthma action plan may predict future planned visits to GP, independent of any additional intervention. We will identify potential baseline variables that might influence outcomes, including age and smoking status, and test for unequal variance in the distribution of these variables in the intervention and control populations.

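### The primary outcome rests on one 10-minute survey chased only by the standard two reminder emails; a one-item follow-up email would reduce reliance on LOCF and could, if enough people answer, bring power to 80%

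*Protocol article*

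**What the plan says.** All places are in the protocol article.

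- **Outcome Measures** defines the primary measure as the number of participants who obtained or updated a written plan with a GP within the 12 months. Table 1 sources it from the pre- and post-study surveys, at baseline and completion only. The monthly surveys described in Table 2 cover symptoms, impact on work and study, and competing demands, not the plan.
- **Intervention and Control** puts the post-study survey at 10 minutes, at 12 months.
- **Study Procedure**: "Email will be the primary channel to communicate with participants for study information and reminders about survey completion". For non-completers, "there will be 2 follow-up emails sent 5 days apart from each other to remind those who have not completed each survey". The post-study survey has no separate rule.
- **Sample Size**: "at least 300 participants with 150 in each arm is needed to detect a 15% point difference", "with an anticipated participant dropout rate approximately 25" per cent.
- **Primary Analysis** follows intention to treat, with LOCF for missing values.
- **Limitations** concedes that "it is possible to observe a high rate of attrition from participants and thus, a significant loss of data". It answers with reminders and with short, convenient monthly questionnaires.

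**The concern.** The primary outcome is one yes/no fact, yet it can be learned only from someone who completes the whole post-study survey. That survey is chased no harder than any of the monthly ones.

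When it is missed, no usable earlier value exists. LOCF can reach back only to baseline, before the period in which the event has to happen. The carried value is then either no event by construction or a record of possession before randomisation. Neither observes the outcome.

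Two things are at stake:

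- **Power**, because imputation of this kind shrinks the expected difference between arms.
- **Bias**, because participants know their allocation and report the outcome themselves, so non-response may differ by arm.

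**Working it through.** **Inputs.** Control 14.4%, intervention 29.4%, two-sided 5%, 80% power, 150 per arm, about 25% dropout (all from Sample Size); 1:1 allocation (Study Design). The share of non-responders who would answer a short email is not in the documents. It is an assumption, varied below. Loss is taken as equal by arm and unrelated to outcome.

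**Step 1: the plan's own figure.** With mean rate 0.219,

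n per arm = [1.960·√(2·0.219·0.781) + 0.8416·√(0.144·0.856 + 0.294·0.706)]² / 0.15²
= (1.1463 + 0.4841)² / 0.0225 = 118.1, so 119 per arm, or 238 evaluable.

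Inflating as 119 × 1.25 gives 149 per arm, 298 in total, which matches the stated 300. Inflating as 119 / 0.75 gives 159 per arm, 318 in total, which does not.

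**Step 2: complete-case power at 25% loss.** 300 × 0.75 = 225 evaluable, 112.5 per arm. Power = Φ[(0.15 − 1.960·SE₀)/SE₁], with SE₀ = 0.5849/√n and SE₁ = 0.5752/√n. At n = 112.5, SE₀ = 0.0551 and SE₁ = 0.0542, so power = Φ(0.773) = 78.0%. The shortfall is 238 − 225 = 13 participants.

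**Step 3: power under LOCF at 25% missing, 150 per arm analysed.**

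- Reading A, missing counted as no plan obtained: 0.75 × 14.4% = 10.8% vs 0.75 × 29.4% = 22.05%. The difference is 11.25 points and power is 75.1%.
- Reading B, missing set to 14.4% in both arms: 14.4% vs 0.75 × 29.4% + 0.25 × 14.4% = 25.65%. The difference is again 11.25 points and power is 68.4%.

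**Step 4: recovering a share of the 75 expected non-responders.**

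| Recovered | Complete case | LOCF, reading A | LOCF, reading B |
|---|---|---|---|
| 0% | 78.0% | 75.1% | 68.4% |
| 10% | 79.4% | 76.8% | 71.0% |
| 20% | 80.6% | 78.3% | 73.4% |
| 25% | 81.2% | 79.1% | 74.6% |
| 30% | 81.8% | 79.9% | 75.8% |
| 50% | 84.0% | 82.7% | 80.1% |
| 100% | 88.5% | 88.5% | 88.5% |

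Break-even for 80% is 13/75 = 17% complete case, just over 30% under reading A, and about 50% under reading B. With a continuity-corrected test, complete-case power at 225 is 72.9%; 264 evaluable are needed, so 39/75 = 52%.

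**The case against.** Several points on the other side stand.

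- **The 25% is not a result of the reminder rule.** A reader might infer that a quarter of the outcomes is lost because chasing stops after two emails. Sample Size gives the figure as an anticipated dropout without a cause, and Limitations links attrition to the length of the study. Some of the 75 may have withdrawn consent, and no email recovers those.
- **The 2-point complete-case gap does not come from Study Procedure.** Dropout is already budgeted in the 300. The figure matches multiplying by 1.25 where dividing by 0.75 was needed.
- **A follow-up email cannot be promised to restore power.** It uses the channel these people have already left unanswered three times. At 10% recovery every column of the table stays below 80%, and at 25% both LOCF columns still do.
- **The article is condensed.** Calling email the primary channel does not rule out others. Question order and the handling of partly completed surveys are operational details that an article may leave out, so no criticism is made of them.
- **Retention is not neglected.** Participants are contacted monthly, controls are offered access after 12 months, and the Concluding Remarks expect the social features to limit attrition.
- **A gain against bias is likely but not guaranteed.** Response to the extra email may itself differ by arm, and a single item is a second mode of measuring a self-reported outcome.

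None of this supplies an outcome value for someone who misses the post-study survey, or makes a baseline value informative about an event during follow-up.

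**Conclusion.** The point holds as an inexpensive improvement worth making. Two reminders per survey is neither an error nor a contradiction. The weakness lies in the combination: a single source for the primary outcome, no extra effort to obtain it, substantial anticipated loss, and an imputation rule that can draw only on baseline.

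The main benefit of the extra email is less dependence on LOCF. Reaching 80% power without further enrolment is possible but conditional. It needs about 13 of 75 non-responders on a complete-case basis, and roughly 30% to 50% of them under the two LOCF readings.

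These figures rest on the plan's own rates, loss of exactly 25% that is equal by arm and unrelated to outcome, and an uncorrected two-sample test of proportions. Reading B also assumes 14.4% baseline possession in both arms. The documents say nothing about the response rate to such an email.

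**What to change.** In Study Procedure, add a rule for the post-study survey only. Participants who have not answered after the second reminder, and have not withdrawn consent, receive one automated email, identical in both arms, with only the primary item: plan obtained or updated with a GP since enrolment, yes or no, and the date. The date keeps late replies within the 12-month window. Report by arm the share of primary outcomes obtained from the full survey, from the single-item email, and by imputation.

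**Cost.** One further automated message in the existing survey system and a short notification to the ethics committees. Surveys already go out automatically, so investigator blinding is unaffected. Recruitment is reported as ongoing; the rule should be in place before the first post-study survey falls due, so that it applies to everyone alike.

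**Downsides to state.** Participants recovered this way provide no other post-study data. The outcome acquires a second measurement mode. Response to the email may differ by arm, which the by-arm report would show.
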